### Hypothesis

EBF will have smaller environmental impact than FF or mixed feeding (MF).

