#### Objectives of the study

Primary objective

Determine the environmental impacts (climate change, water consumption and water scarcity) of EBF, MF and FF of postpartum mothers in their baby’s first month of life, taking into account the accessories used for infant feeding and mother´s diet and food consumption habits.

Secondary objectives:

To calculate the prevalence of EBF, FF and MF after birth, and at 4–6 weeks postpartum.To describe the maternal diet in terms of macro, micronutrients and energy consumed.To compare the calories consumed by according to the type of breastfeeding, lactating mothers (EBF and MF) and non-lactating mothers (FF).To compare feeding types with socio-demographic and clinical data.To compare maternal diet and food consumption habits with feeding type and socio-demographic data.

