### Sample size calculation

For the calculation we took into account both the local data on prevalence of three infant feeding types at month 1 [21] and the data provided by the literature for the footprint for consumption of 1 kg powdered breastmilk substitute for the nearest geographical area. This is 11 kg CO2 equivalents and standard deviation 1 in UK/France [1]. Accepting an alpha risk of 5% and a power of 80%, in a two-tailed test, a minimum of 60 subjects are necessary in the EBF group, 60 in the mixed and in 30 in the FF group to recognize as statistically significant a difference greater than or equal to 0.7 units (One-Way ANOVA menu, StudySize 2.0) [28]. The common standard deviation is assumed to be 1 [1] (One-Way ANOVA menu, StudySize 2.0, [28]).

These 150 women (60 + 60 + 30) are the minimum number we need to recruit. However, at the time of recruitment, we do not know which breastfeeding arm each of the participating women will be in during the follow-up month. From our own previous studies [21], we know that after one month of follow-up, from an initial recruitment of 400 women, some 256 (64%) could be breastfeeding exclusively, 92 (23%) using mixed and 52 (13%) a formula feeding [21]. These expected female counts exceed the required minimums in each arm, and would allow replacement rates for losses during follow-up of up to 35%.

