#### Independent variables

*Socio-demographic and clinical profile:* age; gender; relationship status; country of birth; religion; paid work; TPAL; baby’s birth weight; weeks of gestation at birth; maternity leave; partner leave to care for the baby; maternal pathology and neonatal pathology.*Newborn variables:* type of feeding in hospital and at 1 month of the child’s life; in the case of MF or FF, indicate how much infant formula you feed your baby daily, in ml; number of bottles or syringes of infant formula you give your baby daily; how many ml does each bottle or syringe have.*Breastfeeding accessories:* use (and quantity in case of several) of a breast pump; milk storage containers; bags to store milk; nipple shields; a nursing supplementer; cans of infant formula; bottles; brushes to clean the bottles; a bottle warmer; a bottle sterilizer; paediatric nasogastric tubes; reusable nursing pads and disposable nursing pads.*Mother's nutrition variables**: **a) Eating habits:* type of diet; taking any vitamin supplements; usual place to purchase food, transport of food and distance from home; type of energy used for cooking; members of the family who usually cook and how much of the food is thrown away? *b) Recording of the mother's daily diet (recall 24 h)* [33, 34] (validated in other studies [35, 36]), *and food consumption habits:* type of food: portions, packaging, type of cooking, characteristics of the product (fresh, frozen), origin of the product, condiments and beverages.

The maternal diet will be measured in terms of macronutrients (carbohydrates, proteins and fatty acids in grams), micronutrients (calcium, magnesium and in milligrams, vitamin D in micrograms) and energy consumed in kcal).

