**Fig. 1 Fig1:**
[figure not shown]
Environmental impact factors considered in the GREEN MOTHER I project. Legend: EBF – exclusive breastfeeding; MF – mixed feeding; FF – formula feeding

For the descriptive statistics, the qualitative variables will be described with their absolute and relative frequencies and quantitative variables with their mean and standard deviation or with their median and quartiles. In the comparison of proportions, we will use the Pearson Chi Square test and in the comparisons in quantitative variables the analysis of variance or the Kruscal-Wallis test (with post-hoc analyses), depending on the conditions of application. The level of significance will be 5% and the analyses will be performed with the statistical package STATA v.18.

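### Self-selected feeding groups are compared only by unadjusted tests, which leaves the diet component and the summed impact open to confounding of unknown size and direction

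*Protocol article*

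**What the plan says.** The statistical paragraph of the Data analysis plan (after the Fig. 1 legend) names Pearson chi-square for proportions and, for the rest, "in the comparisons in quantitative variables the analysis of variance or the Kruscal-Wallis test (with post-hoc analyses), depending on the conditions of application". It adds a 5% significance level and the software. The article mentions no regression, stratification, weighting or centre term, and Study Limitations does not mention confounding.

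The rest of the protocol sets up the comparison as follows:

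- **Groups.** Sample size calculation says that a woman's feeding group is not known when she is recruited. The groups form by themselves.
- **Outcome.** Procedure defines the impact of each feeding type as a sum of accessories, artificial milk and the mother's diet. The Data analysis plan also presents feeding type with accessories apart from the mother's diet.
- **Interpretation.** Hypothesis predicts a smaller impact for EBF than for the other two types. Expected outcomes ascribes extra diet impact to compensation for breastfeeding.
- **Covariates.** Independent variables lists "age; gender; relationship status; country of birth; religion; paid work; TPAL", followed by birth weight, gestational age and others.
- **Secondary objectives.** One is "To compare feeding types with socio-demographic and clinical data". Another relates maternal diet to feeding type and to socio-demographic data.

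**The concern.** A woman's age, country of birth, work and parity may influence both how she feeds her baby and what she eats. Her whole diet enters the outcome. An unadjusted difference between EBF and FF mothers would then combine the effect of feeding with pre-existing differences between the women in each group.

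The protocol intends more than a description of the groups. Background asks what greenhouse gas could be saved if breastfeeding were chosen in place of formula. Strengths of the Study says that the results could guide mothers' choices, and Discussion makes them the basis for Phase II. Each of these uses needs a contrast that does not merely reflect who chooses which feeding type.

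**Working it through.** **1. The plan's own figure.** Inputs from Sample size calculation: a two-sided 5% alpha, 80% power, group sizes of 60 EBF, 60 MF and 30 FF, a target of "a difference greater than or equal to 0.7 units", and for the spread "The common standard deviation is assumed to be 1". Power comes from the non-central F distribution with λ = Σ nᵢ(μᵢ − μ̄)²/SD². With means 0 / 0.35 / 0.7 for EBF / MF / FF, μ̄ = (60×0 + 60×0.35 + 30×0.7)/150 = 0.28 and λ = 60×0.0784 + 60×0.0049 + 30×0.1764 = 10.29. Power is 81.9%, and the smallest 2:2:1 design that reaches 80% is 58/58/29. The stated size is reproduced and is not in dispute. The check also shows that the planned analysis is a one-way ANOVA without covariates.

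**2. Can diet matter in the sum?** Background links food consumption to 3,302 L of water per person per day. For 1 kg of powder it gives 4,700 L, or 626 + 6,280 + 524 = 7,430 L. So 1 kg of powder equals 4,700/3,302 = 1.4 to 7,430/3,302 = 2.3 days of one person's dietary water. If 1 kg lasts longer than that, diet is the larger term. These are not ReCiPe or AWARE values and serve only to show scale.

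**3. Illustrative bias.** The documents give no covariate effects, so the inputs are assumed. A binary characteristic shifts the impact by γ SD, and its prevalence differs by Δp between FF and EBF, with MF midway. Bias = γ × Δp. There is no true feeding effect. Group sizes are the plan's expected 256/92/52 from 400 women.

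| γ (SD) | Δp | Bias (SD) | Share of 0.7 | Unadjusted ANOVA rejects |
|---|---|---|---|---|
| 0.3 | 0.1 | 0.03 | 4% | 5.3% |
| 0.5 | 0.2 | 0.10 | 14% | 9.0% |
| 0.8 | 0.2 | 0.16 | 23% | 15.9% |
| 0.8 | 0.3 | 0.24 | 34% | 31.3% |

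For the last row, μ̄ = (92×0.12 + 52×0.24)/400 = 0.0588, which gives λ ≈ 2.94. A total bias of 0.3 SD, which would need a stronger confounder or several acting together, gives 46.5%.

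**4. What adjustment costs.** Suppose that covariates explain a share R² of the FF versus EBF contrast and that adjustment brings no gain from lower residual variance. Effective sizes are n(1 − R²), and power ≈ Φ(0.7/√(1/n₁ + 1/n₂) − 1.96).

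| EBF vs FF | R² 5% | 10% | 20% | 30% |
|---|---|---|---|---|
| 256 vs 52 (expected) | 99.4% | 99.2% | 98.4% | 97.1% |
| 166 vs 34 (after 35% loss) | 95.2% | 94.2% | 91.4% | 87.5% |
| 60 vs 30 (bare minimum) | 86.2% | 84.4% | 80.0% | 74.5% |

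Example: 166×0.7 = 116.2 and 34×0.7 = 23.8, so the standard error is 0.225 and power = Φ(3.11 − 1.96) = 87.5%. The R² values are assumptions.

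**The case against.** **The aim may be descriptive.** The primary objective speaks of determining impacts, and Discussion of exploring them. For the footprint of these groups as they are, unadjusted means are the right quantity. That stands, and those means should be kept. It does not cover the hypothesis, the attribution in Expected outcomes or the choice question in Background.

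**The article is condensed.** A full protocol may specify covariate models, and the statistical paragraph does not rule them out. But this is not a gap left open. The article names its tests, and Sample size calculation names one-way ANOVA. If an adjusted model exists elsewhere, the article should say so.

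**Formula and accessories are shown apart.** This part is computed from recorded amounts and items, so differences in mothers' diets cannot bias it directly. That stands and narrows the point to the diet component and the sum.

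**Centre.** A reader might infer that centre is recorded and ignored. Study design names the sites, but centre is not in the list under Independent variables, and Annex II is not shown. The protocol also trains the midwives in the dietary recall and gives them a food atlas.

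**Expected associations.** A reader might also infer that the authors already expect maternal characteristics to be related to feeding and diet. The objectives only plan to examine those relations.

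**Conclusion.** The concern holds for the diet impact, the summed impact and the comparison of kcal between lactating and non-lactating mothers. The stated tests cannot separate the effect of feeding type from differences between the women who choose it. The size and direction of any bias are unknown. The 4% to 34% range rests on the assumed γ and Δp, and on an SD of 1 that the plan takes from the footprint of 1 kg of powder and does not show to hold for the summed impact.

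A reader might go further and conclude that the breastfeeding advantage could be reversed, or that bias would take up most of it. The documents do not support this. On the illustrated range, a true difference of 0.7 SD would appear as 0.46 to 0.94 SD, so reversal would need much stronger or joint confounding. A calculation in kilograms can be made to look worse: 0.7 L/day × 0.13 kg/L × 11 = 1.0 kg CO2-eq/day, a 40% to 55% saving of 0.40 to 0.55, and a bias of 0.2 to 0.3, or 36% to 75% of the saving. But the intake, the powder concentration and the bias are all assumed there. The 40% to 55% is quoted for the UK, China, Brazil and Vietnam, while Background gives the 11 kg figure for France.

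**What to change.** For the summed impact, the diet impact and the kcal comparison, add a prespecified regression on feeding type with EBF, MF and FF as categories (lactating versus non-lactating for kcal).

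- Adjust for collected characteristics that precede the feeding measured at one month, such as age, country of birth, paid work, TPAL, and gestational age or birth weight. Add recruiting centre if it is recorded.
- Do not adjust for kcal, which lies on the path from lactation to diet impact.
- Use robust standard errors, or a log or gamma model, if impacts are skewed. The current text meets skewness with Kruskal-Wallis, which takes no covariates.
- Report adjusted differences with 95% confidence intervals beside the unadjusted group means, and keep formula with accessories separate from diet.
- Name residual confounding in Study Limitations. Give any bias size only as an illustration with its assumptions.

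The cost is plan wording, some extra analysis in the software already named and a small loss of precision. The named maternal and newborn covariates are already listed for collection. No change to design or recruitment is needed. Power for 0.7 SD falls below 80% only at the bare minimum of 60 versus 30 with R² of 20% (79.96%, shown as 80.0%) or more.

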The manufacture and distribution of industrial infant formula is harmful to the environment, generates polluting waste, and requires energy use to manufacture the formula and packaging materials, and to transport the products, and water use to prepare bottles on a daily basis. Most infant formulas are based on cow's milk. Dairy farms represent the main source of anthropogenic methane emissions. In Europe, livestock farming represents 12–17% (630–863 Mt CO_2_-eq) of total GHG emissions [8].

For an accurate calculation of the environmental impact of breastfeeding, the infant feeding accessories (breast milk pump; milk storage containers or bags, bottles, bottle warmer, and bottle sterilizer, for example) and a theoretical increase of 500 kcal in the diet of the mother must be taken into account [1, 9–12].

There is data on the carbon footprint and water footprint of FF, but there is none on the environmental impact of breastfeeding. The average carbon footprint of FF was estimated to be 9.2, 7, 8.4, and 11 kg CO_2_-eq per kg of formula in New Zealand, USA, Brazil, and France, respectively. The potential carbon savings of BF compared to FF for the UK, China, Brazil and Vietnam is 40–55% [1].

The additional volume of water that a mother consumes while breastfeeding is minor compared to the significant quantities needed for manufacturing formula milk [12]. Research conducted by Pope et al. in the United States demonstrated that producing 1 kg of commercial formula requires 6.6 kg of raw milk, which entails a water footprint (WF) comprising 626 L of blue water for manufacturing, reconstitution, and sterilization, 6,280 L of green water for cow feed, and 524 L of grey water [13]. In Switzerland, Rollins and colleagues estimated that the average WF for whole cow's milk is around 940 L of water per kg of raw milk. When considering that 1 kg of whole milk produces about 200 g of milk powder, the water consumption (WC) amounts to 4,700 L of water per 1 kg of milk powder [14, 15].

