### Procedure

In order to calculate the environmental impacts of the different types of infant feeding, the necessary variables are first to be collected in different questionnaires. Subsequently, the impacts of the types of breastfeeding will be calculated by adding together the impacts associated with the use of accessories, artificial milk and the mothers' diet for each type of infant feeding. The questionnaires are completed by the midwife during the visit with the mother.

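### The planned ANOVA or Kruskal-Wallis comparison of feeding types reflects only variation between women; uncertainty in the shared life-cycle coefficients, above all the formula factor, is absent from its p-values and SDs

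*Protocol article*

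**What the plan says.** Under Procedure, the protocol states that "the impacts of the types of breastfeeding will be calculated by adding together the impacts associated with the use of accessories", artificial milk and maternal diet. Study variables and the Data analysis plan name the methods: IPCC GWP 100 for climate change, ReCiPe for water consumption and AWARE for water scarcity, within a comparative life-cycle study based on ISO 14040 and 14044.

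The statistical part of the Data analysis plan (the text after Figure 1) uses, "in the comparisons in quantitative variables the analysis of variance or the Kruscal-Wallis test", with post-hoc analyses at 5%. Quantitative variables are summarised by mean and SD or by median and quartiles. No step is described that carries uncertainty in the life-cycle coefficients into the group comparison.

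The Background reports that the carbon footprint of formula "was estimated to be 9.2, 7, 8.4, and 11 kg" CO2-eq per kg, for New Zealand, the USA, Brazil and France in that order. The sample size section takes 11 with SD 1 from the literature, per kg of powder, and then states: "The common standard deviation is assumed to be 1".

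**The concern.** Each woman's outcome is modelled: her quantities are multiplied by coefficients and summed. ANOVA and Kruskal-Wallis see how the results differ between women and treat the coefficients as known. Suppose the formula factor is wrong by an amount d. The FF minus EBF difference is then wrong by d times the mean powder intake in FF, whether 30 or 3,000 women are studied. EBF has no formula term to offset it. MF is affected in proportion to its own formula use.

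For the formula component alone the tests cannot react to the factor at all. Multiplying every woman's powder intake by 7 or by 11 leaves the F statistic and the ranks unchanged, so the p-value is identical.

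At stake is how firmly the study can state the size of the EBF advantage. The results are meant to feed Phase II materials and public messages, and a small p-value alone would suggest more certainty than the modelled outcome supports.

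**Working it through.** **1. The plan's own figure.** Inputs from Sample size calculation: two-sided alpha 0.05 and power 80%; 60 women each in EBF and MF; "30 in the FF group to recognize as statistically significant a difference greater than or equal to 0.7 units"; common SD 1. Noncentral-F power for a one-way ANOVA with means 0 / 0.35 / 0.7 (FF at one extreme) at 60/60/30 is 0.819. The smallest 2:2:1 design reaching 80% is 58/58/29. The stated sizes reproduce to within 2 per group.

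This calculation treats the SD of 1 as variation between women, which averages down with n. Its source is a literature figure per kg of powder, not a between-mother SD of the analysed outcome.

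**2. Spread of the formula factor.** Values 9.2, 7, 8.4, 11:
- mean = 35.6/4 = 8.9
- SD = √[(0.09 + 3.61 + 0.25 + 4.41)/3] = 1.67
- midpoint of the range = 9; half-range = 2/9 = 22%

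**3. FF formula component alone.** Relative sampling 95% half-width = 1.96 × CV/√n. Expected FF group: 52 of 400 women (Sample size calculation). The CV of formula intake is not given; 20 to 40% is an assumption.

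| Intake CV | n = 52 | n = 30 |
|---|---|---|
| 20% | 5.4% | 7.2% |
| 30% | 8.2% | 10.7% |
| 40% | 10.9% | 14.3% |

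With 52 women, the CV at which sampling error would match the 22% is 0.222 × √52/1.96 = 0.82. The comparison is one of size only, since a half-range over countries is not a 95% limit. If instead the literature SD of 1 on 11 is read as factor uncertainty (the protocol does not label it so), its 95% half-width is 1.96 × 1/11 = 18%.

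**4. The sample-size scale (per kg of powder, SD 1).** SE of FF minus EBF = √(1/n1 + 1/n2):
- 0.224 at 60/30 and 0.152 at 256/52
- a shared SD of 1.0 is 4.5 to 6.6 times this SE; 1.67 is 7.5 to 11.0 times

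This is not the scale on which mothers will be compared.

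**5. Total per mother, diet included.** Assumption: 0.08 to 0.13 kg of powder per FF infant per day. The shared SD is then 0.08 to 0.13 kg CO2-eq per day (factor SD 1.0) or 0.13 to 0.22 (factor SD 1.67). Ratio = shared SD / (between-mother SD × √(1/n1 + 1/n2)), over both sets of group sizes:

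| Between-mother SD of daily total (assumed) | Ratio, factor to sampling |
|---|---|
| 0.5 | 0.72 to 2.85 |
| 2 | 0.18 to 0.71 |

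The two are equal at a between-mother SD of 0.36 to 0.85 (factor SD 1.0) or 0.60 to 1.43 (factor SD 1.67). The protocol gives neither powder intake nor between-mother SD, so the order is open.

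**6. Water.** The Background gives 626 + 6,280 + 524 = 7,430 L per kg of formula (US study) and 4,700 L per kg of milk powder (Swiss estimate). Product and scope differ, so the ratio of 1.58 is not a measure of uncertainty, but it shows that the source chosen matters there too.

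**The case against.** The strongest reply is that this is detail left to fuller documents. The SAP and full protocol are not shown, the article cites ISO 14040 and 14044, and ANOVA on modelled impacts is valid conditional on the model. That stands as far as it goes: the test is not invalid, and uncertainty work may be planned elsewhere. But the article fixes which test supports the three-group comparison, and that test cannot carry the shared uncertainty.

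Four further limits also stand.

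- **Country differences.** The values 7 to 11 belong to four countries. Part of the spread is real national difference, so it is an upper guide for one Catalan cohort.
- **Single point values are inferred.** The text does not say that one published factor will be entered for all women. Food origin, packaging, cooking and transport are recorded per woman, so diet coefficients could differ between women.
- **Diet-factor errors partly cancel.** They are shared by all three groups and affect a difference only through differences in intake.
- **Diet noise.** The total includes a one-day recall, whose variation between women may dominate.

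A reader might infer that the saving could shrink to 6 to 29%, by taking 40 to 55% as relative to 11 and switching to 7: 1 − 11 × 0.60/7 = 5.7% and 1 − 11 × 0.45/7 = 29.3%. The documents do not support this. "The potential carbon savings of BF compared to FF for the UK, China, Brazil and Vietnam" is the basis of the 40 to 55%, whereas 7 is the USA value and the Background gives 11 for France, so the rescaling mixes countries. Even so, the saving stays positive.

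**Conclusion.** The point holds in limited form. The planned comparison reflects variation between women only. Error in shared coefficients does not fall with n, does not cancel against EBF for formula, and is missing from the p-values and SDs. For the FF formula component the cited range (22% either side of 9, an upper guide) exceeds a sampling half-width of 5 to 11% with 52 women, assuming an intake CV of 20 to 40%.

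Two stronger readings are tempting and are not established. One is that factor uncertainty exceeds sampling error in general: for the total per mother it may be smaller or larger, depending on inputs the protocol does not give. The other is that the direction of the EBF advantage is in doubt: no figure in the protocol shows a reversal. A formula-factor error rescales a positive quantity, so the sign could be at risk only where formula is set against extra maternal diet and accessories. The main risk is to the stated size and precision of the difference.

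This is an inexpensive improvement to the analysis, not a fault that invalidates the test.

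**What to change.** Add to the Data analysis plan, beside the ANOVA or Kruskal-Wallis test and for each of the three outcomes, one of the following:

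- repeat the three-group comparison under low and high plausible formula, diet and water coefficients, for example with 7 and 11 kg CO2-eq per kg as outer bounds for formula and a narrower range if one can be justified for Spain; or
- draw the coefficients by Monte Carlo, with each draw common to all women, and report the 2.5 to 97.5% interval of the group differences.

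Report the range of EBF, MF and FF differences next to the p-values, with the formula and accessories part shown separately from diet. State in advance that the claim of a smaller EBF impact, and its size, will be qualified if it does not hold over that range.

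No new data are needed. The cost is extra analysis work, wider intervals and possibly a more cautious conclusion.
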